### 3.10 Cost analysis

Using the broadest 'societal' perspective, we will estimate the total cost of treatment per child treated and per child recovered. The relevant types of costs will include direct medical costs [provider time, capital costs (building space, equipment), consumables (medical supplies, medications), and overhead (electricity, water, and maintenance)], direct non-medical costs [fees for participant travel, food, lodging, and child care], and indirect costs [time spent seeking care] during both inpatient and outpatient care. Data on resources used will be collected on standardized forms and supplemented with key informant interviews with study staff and accounting records. An incremental cost-effectiveness ratio (ICER) will be calculated as the difference in cost between groups divided by the difference in effectiveness between treatment strategies, expressed in dollars per unit of effect (e.g. per case treated, case recovered).

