#### 1.4 Preliminary studies

The proposed monthly schedule of follow up will involve an extension of the period between which the child receives a health assessment by a health worker. During this time, caregivers will be asked to monitor the clinical and anthropometric status of the child at home and return to the health facility for medical attention upon development of any clinical sign of concern.

To support caregivers in these tasks, culturally-appropriate educational tools and messages, including materials for facility-based instruction (e.g. posters, pictorial flip charts), as well as for home-based use (e.g. pocket pictorial cards), were developed with MSF-France and the LASDEL in 2014. Tools covered the key topics of: a) home-based MUAC measurement; b) clinical surveillance of key danger signs or symptoms; and c) appropriate storage and distribution of the monthly therapeutic ration.

A mixed-methods pilot study of the educational tools and key messages, as well as feasibility of a monthly RUTF ration, was completed in 2015 in Madarounfa, Niger. The validity and reliability of caregiver MUAC measurements, and the retention of key messages, were assessed using standardized questionnaires administered pre- and post- intervention. Weight gain and unannounced home spot checks were used to assess home utilization of the monthly ration. Focus group discussions and semi-structured interviews with caregivers, heads of households, and health workers were used to assess the suitability of the educational tools and key messages. Results from this pilot study suggested that 1) caregivers satisfactorily retained information on clinical danger signs and the correct method to measure MUAC immediately and 28-days following a brief training and 2) the provision of a monthly ration of RUTF can be both feasible and safe, with the correct home storage and utilization of RUTF observed in the majority of households visited early in treatment, and very few cases of weight loss or hospitalization (results in press).

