- Weight gain (g / kg / day), defined as the difference in weight (g) from admission to week 4, to week 8 and to discharge divided by weight on admission (kg) and number of days between admission and week 4/week 8/discharge among recovered children.
  - Defaulting, defined as 3 missed scheduled facility visits in the weekly follow-up group and 1 missed scheduled facility visit in the monthly follow-up group.
  - Relapse, defined as maternal report of admission to any therapeutic feeding program within 3 months of discharge from the index admission.
  - Program coverage, defined as single coverage of SAM treatment, estimated in the weekly and monthly follow-up groups using the SQUEAC methodology.
  - Cost per child treated and per child recovered, defined using the societal perspective to identify all provider and caregiver costs associated with treatment.

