### 3.0 METHODOLOGY

#### 3.1 Study design

This study will be conducted as a stratified cluster randomized trial of a monthly schedule of follow up in the treatment of uncomplicated SAM among children aged 6 to 59 months. The unit of randomization will be the outpatient therapeutic feeding center. The 10 health centers supported by UNICEF will be stratified by size ( $\pm 500$  admissions per site), and centers within a stratum will be randomized in a 1:1 ratio to one of two schedules of treatment: (1) standard weekly visits or (2) monthly visits with support for home-based surveillance.

Distribution of the therapeutic feeding rations, as well as medical and anthropometric surveillance, will take place on a weekly or monthly basis until discharge according to the random assignment of the site. Caregivers in the monthly visit group will receive additional instruction at admission regarding home-based MUAC measurement and clinical surveillance.

Regardless of intervention assignment, all children with uncomplicated SAM will receive standard medical care on admission as per national guidelines, and a home visit 3 months following discharge from the nutritional program. Additional data collection, including coverage assessment and economic costing analysis will be used to address the secondary objectives related to the evaluation of coverage and cost-effectiveness, respectively.

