### 5.2 Risk minimization and benefits

Personnel involved providing clinical care to participants include Ministry of Health program staff and study staff. All such personnel are trained health care personnel and all (e.g. Ministry of Health program staff and study staff) will be provided additional training by the study team at the start of the study and regularly throughout the study duration. The additional training provided by the study team to health care personnel and study staff will refresh best practices and procedures to improve detection of clinical complications and will minimize risk associated with complications during treatment.

In addition, all caregivers will be instructed to return to the health center between scheduled visits if any clinical sign of concern develops at home. Encouragement for caregivers to return to the health center will promote timely management of any complication and will minimize risks associated with complications during treatment.

Caregivers assigned to a health center with a monthly schedule of follow-up will further receive additional training (30 minutes at the admission visit) and take-home pictorial tools for reference on how to assess clinical danger signs at home. This training specifically includes a presentation of the 9 clinical dangers signs for which care should be sought (e.g. diarrhea, vomiting, fever, lethargy, lack of appetite, edema, cough, difficulty breathing convulsions), as well as instruction on the procedure to measure the child's anthropometric status at home using a modified MUAC tape. The recommended home surveillance of these 9 clinical danger signs and anthropometric assessment is equivalent to the surveillance of key clinical danger signs and anthropometric assessment conducted by health care personnel at the health facility during routine care. Caregivers' knowledge of these signs and procedures will be assessed after training to insure complete and accurate understanding before continuing at home. Under the assumption that the training and take-home materials will allow caregivers to monitor children for key danger signs in an equivalent manner to that observed in a health facility, we expect no increased risk to children in the monthly follow-up group associated with monthly schedule.

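### The cost analysis promises all caregiver costs but lists only time seeking care, so the extra home-surveillance time in the monthly arm is valued at zero

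*Protocol*

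**What the plan says.** Section 2.0 lists cost per child treated and per child recovered as a secondary endpoint, "defined using the societal perspective to identify all provider and caregiver costs associated with treatment". Section 3.10 repeats the breadth of that claim: "Using the broadest 'societal' perspective, we will estimate the total cost of treatment per child treated and per child recovered".

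The cost list in section 3.10 is narrower. For caregivers it has "direct non-medical costs [fees for participant travel, food, lodging, and child care" and "indirect costs [time spent seeking care] during both inpatient and outpatient care". Time at home is not named under either item. The ICER is the between-group cost difference over the between-group difference in effect.

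The intervention itself moves work to the home. Section 1.4 says that under the monthly schedule "caregivers will be asked to monitor the clinical and anthropometric status of the child at home". Section 3.1 gives the instruction to one arm: "Caregivers in the monthly visit group will receive additional instruction at admission regarding home-based MUAC measurement and clinical surveillance". Section 5.2 says that the recommended home surveillance "is equivalent to the surveillance of key clinical danger signs and anthropometric assessment conducted by health care personnel at the health facility during routine care".

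**The concern.** The endpoint definition and the cost list disagree on scope, and the item that falls between them is the task that the monthly strategy hands to caregivers. Facility surveillance is costed twice over, as provider time and as caregiver time spent attending. The home surveillance that stands in for it carries no cost.

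Monthly follow-up is expected to lower the caregiver's cost of attending (section 1.1), and that reduction will be measured. The offsetting increase at home will not. A reader of the published ICER would take it as the full societal comparison that the protocol announces, when one component of it is tilted in a known direction. The data also have to be collected during follow-up: the supplementary sources in section 3.10, staff interviews and accounting records, are unlikely to hold caregivers' time at home.

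**Working it through.** The protocol states no cost, time or ICER figure, so there is nothing to reproduce. The check has two parts.

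**Direction, from the definitions**

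Let H_m and H_w be caregiver hours per child on home surveillance in the monthly and weekly arms, and let v be the value of an hour. Write D = C_m − C_w for the full societal cost difference. If home time is left out of both arms, the analysis records

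D_recorded = D − v × (H_m − H_w).

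- H_w is not zero. Section 1.1 says that caregivers in ordinary outpatient care already watch the child's condition between weekly visits, and sections 3.5 and 4.6 tell all caregivers to return if a sign of concern appears.
- H_m should exceed H_w. Home MUAC measurement, training on nine danger signs and take-home tools are given at monthly sites only (sections 3.1, 3.5, 4.5, 5.2).
- With H_m > H_w, D_recorded is lower than D, so the ICER numerator is shifted in favour of monthly follow-up.
- The "additional training (30 minutes at the admission visit" takes place at the facility, can be captured as time seeking care, and is not part of the omission.

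**Size, from assumptions**

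From section 4.6: weekly visits against visits at weeks 4, 8, 10 and 12. For a child discharged at week 8, that is 8 visits against 2, so 6 averted.

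Assumed, because the protocol gives no values: home checks of 5 minutes once a week, 5 minutes daily or 15 minutes daily; 2, 4 or 6 caregiver hours per visit, travel and waiting included.

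Omitted hours = minutes per check × checks per week × 8 ÷ 60. Saved hours = 6 × hours per visit, which gives 12, 24 or 36 h.

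| Home checks | Omitted hours | Share of 12 h saved | Share of 24 h saved | Share of 36 h saved | Break-even visit length |
|---|---|---|---|---|---|
| 5 min weekly | 5 × 1 × 8 ÷ 60 = 0.67 | 6% | 3% | 2% | 0.67 ÷ 6 = 0.11 h |
| 5 min daily | 5 × 7 × 8 ÷ 60 = 4.67 | 39% | 19% | 13% | 4.67 ÷ 6 = 0.78 h |
| 15 min daily | 15 × 7 × 8 ÷ 60 = 14.0 | 117% | 58% | 39% | 14.0 ÷ 6 = 2.33 h |

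These figures set H_w to zero, so each overstates the increment by whatever weekly-arm caregivers spend. Omitted time exceeds saved time only in the extreme corner, daily 15-minute checks with 2-hour visits. The picture is much the same at other stays: at week 4 (3 visits averted) the range is again 2% to 117%, and at week 12 (8 averted) it is 2% to 131%.

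**The case against.** Section 3.10 introduces its list with wording that can be read as non-exhaustive, the items are short bracketed labels, and the standardized costing forms are not shown. The endpoint definition already commits to all caregiver costs, so the list may be only a loose summary, and a costing plan may itemise home time. That is possible. But the indirect-cost bracket names a single item, and following it as written contradicts the endpoint. If the forms already ask about home time, one line in section 3.10 settles the matter.

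A second objection is that many danger signs, such as vomiting, cough or fever, are noticed in the course of ordinary child care and may displace no other work. This stands as a reason why the omitted cost could be small. It applies less to MUAC measurement, which is a separate act.

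A reader might go further and infer that home monitoring is a cost in the monthly arm alone, or that monthly follow-up is in truth the dearer option. The documents support neither. Section 1.1 describes monitoring between weekly visits too, so only the increment is at issue. The percentages above are shares of caregiver visit hours, not of total societal cost, which also holds provider time, capital, consumables, overhead, travel, food, lodging, child care and inpatient care. Nor do the documents set daily checks, so a figure that presumes them cannot serve as the estimate.

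**Conclusion.** The inconsistency is real, and its direction follows from the protocol's definitions, provided that monthly-arm caregivers spend more time on home surveillance than weekly-arm caregivers. The cost comparison then favours monthly follow-up by the value of that extra time.

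The magnitude is unknown. The range of about 2% to 117% of caregiver visit time saved rests wholly on assumed check frequency, check duration and visit length at an 8-week stay, before any deduction for weekly-arm monitoring. The share of total societal cost and the effect on the ICER cannot be computed from the protocol, and a reversed cost ranking is not shown. The point bears on one component of a secondary endpoint; it does not touch the recovery comparison. It is a cheap improvement.

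**What to change.** In section 3.10, define indirect costs as caregiver time seeking care plus caregiver time on home-based surveillance, MUAC measurement included, with both valued at the same hourly rate.

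Collect the home time with the same one or two questions in both arms. Asking monthly-arm caregivers only would replace one one-sided count with another. Existing contacts are enough: caregivers already report daily supplement use at every follow-up visit, and a questionnaire on home surveillance is given in both groups at discharge (section 4.6).

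Report cost per child treated, cost per child recovered and the ICER with and without this item. If the time is not collected, narrow the claims in sections 2.0 and 3.10 to a perspective that excludes unpaid caregiver time at home, and say so when the ICER is reported.

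The cost is one line of protocol text and one or two questions on an existing form. The drawbacks are that the time is self-reported and that the apparent saving from monthly follow-up may shrink.

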## 1.3 Innovation and relevance for the community-based management of SAM

The outpatient management of SAM has been recommended by the World Health Organization, WFP, UN Standing Committee on Nutrition and UNICEF since 2007. However, reliance on a weekly schedule of follow up limits operations to areas where access and frequent visits to a health facility are possible and potentially reduces the number of children receiving treatment. In contexts where weekly follow up is not feasible (e.g. Chad where access was limited due to heavy rains; Somalia where access is reduced due to high insecurity), programs have been forced to curtail operations, resulting in fewer children receiving treatment. Similarly in contexts where the absolute number of children needing treatment is very high (e.g. northeastern Nigeria), the burden of the traditional schedule of follow up can limit coverage and reduce program impact. To our knowledge, no program has implemented a reduced schedule of follow up (beyond biweekly visits) and documented safety or efficacy. This proposal therefore represents innovation as this is the first time a strategic reduction in the schedule of follow up will be implemented and evaluated within the community-based treatment model.

This study is intended to provide programs with greater flexibility to consider more innovative models of treatment and to extend operations into areas previously unsuitable for treatment programs. If the results of this study can confirm that monthly visits in the treatment of uncomplicated SAM can achieve similar rates of nutritional recovery as standard weekly visits, programs will have the evidence needed to consider adopting a reduced schedule of follow up and provide treatment in a greater number of settings. Evidence provided by this study could support increased coverage in existing programs, as a reduced schedule of follow up in an existing program could decrease the program burden per child and allow for an increase in the proportion of children covered using the same or fewer resources. These results could also allow more flexible and innovative programming in new settings where the standard protocol has been impractical, including contexts with nomadic populations, difficult geographical access, conflict or high incidence of malnutrition.

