### 3.7 Power calculations

Ten outpatient therapeutic feeding centers in this setting can be expected to admit total of 3,500 children for the treatment of uncomplicated SAM over 12 months (3,777 children admitted at 10 facilities in 2016). Assuming a baseline risk of nutritional recovery in the weekly

follow-up group of 0.80, intraclass correlation of 0.002 and significance level of 0.05 using the one-sided Score test, and allowing for 20% loss to follow up, a sample size of 350 children per health facility (2100 per group) will achieve 88% power to detect a non-inferiority margin difference between the group proportions of -0.05.

|                        | Difference in recovery between weekly vs. monthly follow up groups (n = 350 per site) |                  |                  |
|------------------------|---------------------------------------------------------------------------------------|------------------|------------------|
| Intraclass correlation | $\Delta = -0.15$                                                                      | $\Delta = -0.10$ | $\Delta = -0.05$ |
| 0.001                  | 1.00                                                                                  | 1.00             | 0.94             |
| 0.002                  | 1.00                                                                                  | 1.00             | 0.88             |
| 0.01                   | 1.00                                                                                  | 0.97             | 0.54             |

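### Section 3.10 sets an incremental cost-effectiveness ratio whose treated-case unit has a zero denominator and whose recovery version is unstable if recovery is similar

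*Protocol*

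**What the plan says.** Section 3.10 of the protocol opens with average societal costs by child treated and by child recovered. That matches the economic endpoint in Section 2.0: "Cost per child treated and per child recovered, defined using the societal perspective".

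Section 3.10 then adds an incremental measure. The ratio is "calculated as the difference in cost between groups divided by the difference in effectiveness between treatment strategies", and it is to be "expressed in dollars per unit of effect (e.g. per case treated, case recovered"). The section gives no rule for a denominator that is near zero or negative.

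Two other places show what denominator to expect. Section 1.3 wants to learn whether monthly visits "can achieve similar rates of nutritional recovery as standard weekly visits". Section 3.7 sets recovery in the weekly "follow-up group of 0.80", an "intraclass correlation of 0.002 and significance level of 0.05 using the one-sided Score test", and a "non-inferiority margin difference between the group proportions of -0.05". It does not state the true difference in recovery at which power was computed.

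**The concern.** An ICER needs a denominator that is a real effect difference, clearly away from zero. The two example units fail for different reasons.

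- **Treated cases.** This is a structural fault. Being treated is what defines an enrolled child in either group, so the per-child difference is zero by construction and the ratio is undefined.
- **Recovered cases.** This is a sampling fault. If recovery is about equal, the denominator is mostly noise around zero. Suppose monthly visits are cheaper. A small chance gain in recovery gives a negative ratio (cheaper and better). A small chance loss gives a positive one (money saved per recovery forgone). A negative ratio would also arise if monthly visits cost more and recovered fewer children. Neither the sign nor the size can then be read by itself.

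At stake is whether the incremental part of the cost-effectiveness objective yields a usable number in the situation the trial hopes for.

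**Working it through.** **Inputs.** From Section 3.7: weekly recovery 0.80, intraclass correlation (ICC) 0.002, one-sided 0.05, margin -0.05, 350 children per site, 20% loss. From Sections 3.1 and 3.6: 10 centers, 1:1 within strata, taken here as 5 per group. That gives 5 x 350 = 1,750 per group. Section 3.7 also states 2,100, which would be 6 x 350.

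**Step 1: reproduce the plan's power.** Assume recovery of 0.80 in both groups.

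- Design effect = 1 + 349 x 0.002 = 1.698.
- Variance of the difference = 2 x 0.80 x 0.20 / 1,750 x 1.698 = 0.000310, so SE = 0.0176.
- The score test with this inflation gives power 0.883 (stated 0.88). At ICC 0.001 it gives 0.938 (0.94). At ICC 0.01 it gives 0.538 (0.54), and 0.966 (0.97) for the -0.10 margin.

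So a true difference of zero, with 1,750 per group and no loss removed, reproduces the table.

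**Step 2: the treated-case unit.** Per enrolled child, the treated proportion is 1 in both groups: 1 - 1 = 0. Dividing the cost difference by zero gives nothing. If group totals are used instead, the denominator is the difference in admissions between two sets of five centers. Stratifying by size limits that difference but does not make it a treatment effect.

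**Step 3: the recovery unit at no true difference.** P(|d| < 0.01) = 2 x Phi(0.01 / SE) - 1.

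| Scenario | SE | P(within 1 point of zero) |
|---|---|---|
| 5 x 350, ICC 0.002 | 0.0176 | 0.43 |
| 5 x 280 (20% lost), ICC 0.002 | 0.0189 | 0.40 |
| 6 x 350 (2,100 per group), ICC 0.002 | 0.0161 | 0.47 |
| 5 x 350, ICC 0.01 | 0.0287 | 0.27 |

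The last row is lower because the estimate is noisier, not because the ratio is steadier; Step 4 shows this.

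**Step 4: chance of the wrong sign when the true difference is not zero.** P = Phi(-true difference / SE).

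| True difference | 5 x 350, ICC 0.002 | 5 x 280, ICC 0.002 | 5 x 350, ICC 0.01 |
|---|---|---|---|
| 1 point | 0.29 | 0.30 | 0.36 |
| 2 points | 0.13 | 0.15 | 0.24 |
| 3 points | 0.04 | 0.06 | 0.15 |
| 5 points | 0.002 | 0.004 | 0.04 |

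**Step 5: illustration in money.** The protocol gives no cost figures, so these are assumptions. Take a saving of $20 per child with SE $3, independent of the recovery estimate.

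- An observed gain of half a point gives -20 / 0.005 = -$4,000 per recovery. A loss of half a point gives -20 / -0.005 = +$4,000. The two data sets are almost the same.
- By simulation at no true difference (5 x 350, ICC 0.002), the ICER's 95% range is about -$18,200 to +$18,300.
- Incremental net benefit is (value per recovery x recovery difference) minus cost difference. It contains no ratio. Its mean is $20 at every value. Its SD is the square root of 3^2 + (value x 0.0176)^2: $3.5 at $100 per recovery, $9.3 at $500 and $17.9 at $1,000. The chance that it is positive is 1.00, 0.98 and 0.87.
- At $500 per recovery, an assumed saving of $10 (SE $2) gives 0.87 and one of $50 (SE $8) gives 1.00.

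**The case against.** **The ICER is not the stated endpoint.** A reader might infer that the whole cost-effectiveness objective would come out undefined. The protocol does not support that. The objective and endpoint in Section 2.0, and the first sentence of Section 3.10, concern average costs per child treated and per child recovered. Those stay well defined when recovery is equal. This stands and limits the point to the incremental measure.

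**Zero difference is not stated.** A reader might infer that the design declares recovery equal. It does not: equal recovery is implied by the power table and by the aim in Section 1.3, and it is a usual planning value for non-inferiority. A real difference is possible, and from about 3 points the sign is mostly right. This stands too.

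**Some striking figures are not specific to this trial.** An even split of signs, or a very wide spread in the ratio's size, holds for any estimate centered on zero. Only the results that use the SE say something about this design.

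**Wrong ranking is not shown.** A reader might infer that the schedules would be ranked wrongly. No rule in the protocol ranks them by the ratio's sign, and both differences must be computed anyway, which identifies the quadrant.

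**Treated cases might be meant at program level.** The units are only examples, and Section 1.3 does speak of treating more children with the same resources. But Section 3.10 does not say so, coverage is a separate endpoint in Section 2.0, and an admissions difference across five centers per group would be mostly center mix. The wording still needs correcting.

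**Intervals and bootstrap details may sit in an analysis plan.** Agreed; their absence is not the point. The ratio and its units are fixed in the protocol.

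**Conclusion.** The point holds in a limited form. Treated cases do not work as the effect unit of an ICER on any per-child reading, and this needs no assumption about recovery. The recovery ICER is unstable if true recovery differs by little: with SE 0.0176 to 0.0189, the estimate is within 1 point of zero in 40-43% of trials at no true difference, and the sign is wrong with probability 0.29 at 1 point and 0.13 at 2 points. The problem fades from about 3 points at ICC 0.002, and more slowly at ICC 0.01.

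These figures rest on five centers per group, 350 or 280 children analyzed per center, recovery near 0.80, and a normal approximation. The dollar amounts are illustrative only.

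Importance is minor to moderate. Only a secondary economic objective is affected; the primary analysis and the average-cost endpoints are not.

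**What to change.** In Section 3.10:

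1. Delete treated cases as an effect unit for the ICER. Keep cost per child treated only as an average by group, as already planned.
2. Report the difference in mean societal cost per child, with an interval that allows for only five clusters per group.
3. Present the recovery comparison as incremental net benefit over a stated range of values per recovered child, or show the cost and effect differences jointly on a cost-effectiveness plane.
4. Give the ICER per recovered child only as a supplement when the recovery difference is clearly non-zero, by a rule written down in advance.

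This changes wording and uses cost and recovery data already collected. The cost is that a range of values per recovered child must be stated, and the protocol offers none at present. The plane avoids that requirement but leaves the trade-off to the reader.
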